### Study objectives and endpoints

The primary objective of the IIPOP study in patients with synchronous and limited PC arising from gastric carcinoma, is to estimate 2-year overall survival (OS). Each treatment arm will be compared to theoretical rates using a design with one single stage (no interim analysis of the primary criterion of efficacy).

The secondary endpoints are:

– morbidity and toxicity: postoperative mortality (D30 or until discharge from hospital), acute toxicity (D30 or until discharge from hospital) according to the NCI-CTC-AE toxicity scale version 4.0 [22], and side effects more specifically associated with catumaxomab: systemic inflammatory syndrome (SIRS), hepatotoxicity, skin reaction of an allergic type (temperature, level of haemoglobin, hepatic profile (ALAT, ASAT, alkaline phosphatases, bilirubin) on D3, D6 and D9),

– the 2-year peritoneal relapse rate,

– the 2-year relapse-free survival rate,

– 5-year overall survival.

Translational research based on an immunological analysis will be performed, to determine the immunological markers of the efficacy of catumaxomab, to correlate these markers with clinical efficacy.

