### Assessments and follow-up

During the screening period, patients will be assessed for their eligibility to be included in the IIPOP study. Inclusion and exclusion criteria will be assessed by the investigator.

Morbidity and toxicity (D30 or until discharge from hospital) will be evaluated during the intraperitoneal treatment and the postoperative period. The severity of complications (Grade I-V) [24] will be assessed and adverse events will be categorized using the CTCAE version 4.0 [22].

The planned duration of follow-up is 5 years, with three-monthly follow-up visits consisting of a physical examination, laboratory tests (including tumour marker determination) and imaging (alternating between chest and abdomino-pelvic CT scan and abdominal ultrasound), over the first 2 years. From 2 to 3 years, monitoring will be done every 4 months, and after 3 years, every 6 months.

For the immunological monitoring, samples of peritoneal fluid will be collected at the beginning of the surgery, at the end of the procedure and during IP treatment on D2 and D6. Analysis of cellular immunity (qualification and quantification of cells (T cells, NK cells, macrophages, dendritic cells), of the cytokine profile and of the cytotoxicity (cell death) will be done on peritoneal fluids. Blood samples will be collected at the beginning of the surgery, just before discharge of hospital and 4 +/-1 months later, to study the innate and specific immunological response and the cytokine profile.

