#### Statistical analysis plan

The main analysis of efficacy in each treatment arm will be carried out once all the patients in the said arm have been followed up for 2 years. Overall survival is defined as the period between the date of surgery and the date of death for whatever reason or the date of the latest news for patients who are still alive. Relapse-free survival is defined as the period between the date of surgery and the date of the first event (relapse or death for whatever reason) or the date of the latest news for patients who are still live and are free of recurrence. The time to a peritoneal relapse is defined as the time between the date of surgery and the date of the peritoneal relapse. Patients who die but were free of any peritoneal relapse at the time of death will be censored on the date of death. Patients who are still alive without a peritoneal relapse at the time of the most recent news will be censored on the date of the latest news. Overall survival, relapse-free survival and peritoneal relapse rates will be estimated using the Kaplan-Meier method. The rates at 2 years and 5 years will be estimated with their 95% confidence interval using the Rothman method. If, at the end of the trial, both treatment arms are considered to be promising, their efficacy and toxicity will be compared. However, as the trial was not planned to perform these comparisons, the power of these comparisons will be low and they may only be considered as exploratory analyses to be confirmed by subsequent studies.

The rates of grade 3-4 acute toxicity and the rates of early reinterventions as well as their 95% confidence intervals will be estimated in both treatment arms. This will also be carried out for the rate of the side effects more specifically associated with catumaxomab.

An intention to treat analysis will be conducted: all randomised subjects will be taken into account in the analysis depending on their randomisation group including those incorrectly included or those who do not meet protocol inclusion criteria. All the randomised patients will be analysed for the toxicity of the procedure. In order to be considered suitable for assessment of the toxicity of the intraperitoneal infusion of catumaxomab, patients must have received at least one injection.

The Biostatistics and Epidemiology Unit of the Institut Gustave Roussy is responsible for data management and analysis of this trial.

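### Relapse-free survival and time to peritoneal relapse are censored at the same latest-news date as overall survival, not at the last disease assessment, so time in which relapse was no longer looked for can count as relapse-free

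*Protocol article*

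**What the plan says.** The Statistical analysis plan section of the article describes the censoring date in the same terms for three endpoints.

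- OS runs from surgery to "date of death for whatever reason or the date of the latest news for patients who are still alive".
- RFS runs to first relapse or death, or to "the date of the latest news for patients who are still live and are free of recurrence".
- For time to peritoneal relapse, patients still alive "without a peritoneal relapse at the time of the most recent news will be censored on the date of the latest news". For deaths, "Patients who die but were free of any peritoneal relapse at the time of death will be censored on the date of death".

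The estimator is common to all three: "Overall survival, relapse-free survival and peritoneal relapse rates will be estimated using the Kaplan-Meier method". Study objectives and endpoints lists "the 2-year peritoneal relapse rate" and the 2-year RFS rate as secondary endpoints.

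Assessments and follow-up sets out how relapse is looked for: visits every three months with a physical examination, laboratory tests including tumour markers, and "imaging (alternating between chest and abdomino-pelvic CT scan and abdominal ultrasound), over the first 2 years". Visits are four-monthly in the third year and six-monthly after that.

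**The concern.** A report that a patient is alive is complete information for OS. It says nothing about peritoneal disease unless the patient was also assessed. If the latest-news date is later than the last assessment, the interval between them enters the Kaplan-Meier risk set as time free of relapse, although no relapse could have been recorded in it.

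The two dates can separate in two ways.

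- **Vital status only.** The primary decision counts patients alive at 2 years, so centres have a reason to obtain vital status for patients who no longer attend. A patient with clear imaging to month 12 and one call at month 24 would be scored 24 months free of relapse, of which 12 were observed.
- **Earlier relapse elsewhere.** For the peritoneal endpoint, a patient whose first relapse is in the liver stays at risk. With liver relapse at month 6, no further scheduled imaging and news of survival at month 20, the patient contributes 20 months free of peritoneal relapse, of which about 6 were observed.

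At stake are two secondary endpoints. The peritoneal one describes most directly what the intraperitoneal treatment is meant to achieve, and a peritoneal relapse missed in this way is not recovered later, because the patient's death is itself censored. In RFS the death is at least counted.

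**Working it through.** **The plan's own figure.** The article gives no planning figure for RFS or peritoneal relapse. Its only reproducible figures belong to the primary rule. With 20 patients and success at 9 or more alive, the exact binomial gives P(X ≥ 9 | 0.30) = 0.1133 and P(X ≥ 9 | 0.55) = 0.8692, so the type II error is 0.1308. These match the stated 11% and 13%. The rule does not use the relapse endpoints, so this point does not touch it.

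**Inputs for the relapse endpoints.** From the article: the censoring rules, the Kaplan-Meier estimator and the three-monthly schedule. Assumed, because the article gives no values: the net 2-year peritoneal relapse probability p (40% or 60%), exponential relapse times, and a fraction f of patients who stop assessment at a time uniform over 0 to 24 months while vital status stays known.

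**Closed form.** Under the written rule, a patient who stops assessment can have a relapse recorded only before stopping. Averaged over the uniform stopping time, that probability is

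m = 1 − p / [−ln(1 − p)].

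- p = 0.60: m = 1 − 0.60/0.9163 = 0.3452
- p = 0.40: m = 1 − 0.40/0.5108 = 0.2170

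The written rule then estimates (1 − f)p + f·m, which is short of p by f(p − m). Deaths independent of relapse do not change this, because they are censored.

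| f | p = 60%: estimate (shortfall) | p = 40%: estimate (shortfall) |
|---|---|---|
| 0% | 60.0% (0) | 40.0% (0) |
| 5% | 58.7% (1.3) | 39.1% (0.9) |
| 10% | 57.5% (2.5) | 38.2% (1.8) |
| 20% | 54.9% (5.1) | 36.3% (3.7) |
| 30% | 52.4% (7.6) | 34.5% (5.5) |

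A simulation of 400,000 patients agrees to within 0.2 points. Censoring at last imaging returns about 60% and 40% throughout.

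**RFS.** With p = 60% and no other deaths, simulated 2-year RFS under the written rule is 41.3% to 47.8% for f = 5% to 30%, against a true 40.0%. With 20% other deaths it is 33.2% to 38.3%, against 32.1%.

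**A more detailed model.** Assume that 50% relapse by 2 years, 70% of relapses are peritoneal, detection is at the next three-monthly visit, median survival after relapse is 12 months, and f = 20%.

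- Peritoneal rate: 0.339 with full assessment, 0.305 under the written rule, and 0.339 when censored at last assessment.
- RFS event rate: 0.500 with full assessment and 0.469 under the written rule. Censoring survivors at last assessment while counting every death overshoots, at 0.513. Also censoring deaths that follow two or more missed visits at the last assessment gives 0.502.

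**The opposing effect.** Censoring deaths without peritoneal relapse makes one minus Kaplan-Meier exceed the cumulative incidence. With p = 60% and full assessment, it is 59.8% against 54.6% if 20% die of other causes by 2 years, and 60.0% against 48.8% if 40% do. With 20% other deaths and f = 20% the two effects nearly cancel (54.8% against 54.6%). With 40% other deaths and f = 30% the estimate is still above the cumulative incidence (52.3% against 48.8%).

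**The case against.** **The term is undefined.** For the relapse endpoints the text attaches disease status to the date: the patient must be free of recurrence, or without peritoneal relapse, at the latest news. It could mean the last news on disease status, in which case a call reporting only survival would not move the date. This reading is possible. But the same phrase is used for OS, where it can only mean last known alive, and nothing gives it a second meaning. The rule is written in the article, so this is a stated choice and not a detail left to an unseen document.

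**The bias may be zero.** Examination, markers and imaging fall at the same visits, so for patients who keep to the schedule the two dates nearly coincide. This stands: every non-zero figure above rests on an assumed rate of stopping assessment.

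**A reader might infer that the published peritoneal relapse rate will be too low outright.** The documents do not support that. The shortfall is relative to the same Kaplan-Meier estimate censored at last assessment. Against cumulative incidence, the censoring of deaths pushes the other way and may dominate. The cancellation depends on unknown rates, however, so it is no safeguard, and RFS has no such offset because it counts deaths.

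**The effect is small beside the noise.** At a rate of 0.34 with 20 patients, the approximate 95% half-width is 1.96 × √(0.34 × 0.66/20) = 0.21, or 21 points. A shift of 2 to 5 points is at most about one patient per arm (0.05 × 20 = 1). This also stands, although a wide interval does not correct a systematic error.

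**The remedy has its own assumption.** Censoring at last assessment is unbiased only if stopping is unrelated to relapse. Patients who stop attending because they are deteriorating would break it. For RFS, setting aside late deaths departs from counting death from any cause, which is why that version should not replace the main analysis.

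**Conclusion.** The point holds in a conditional form. As written, the rule lets time without disease assessment count as relapse-free for patients known to be alive. Relative to the same estimator censored at last assessment, the 2-year peritoneal relapse rate is then too low by about 2 to 3 points if 10% stop assessment and about 3 to 5 points if 20% do. Two-year RFS is too high, by about 3 points (0.531 against 0.500) in the detailed model at 20%. If nobody stops assessment there is no bias.

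These sizes rest on assumed relapse rates, uniform stopping times and stopping unrelated to relapse. The direction of the net error against cumulative incidence is not established. Only secondary endpoints are affected, and the primary decision on OS is unchanged. The change is still worth making because it is cheap and removes an avoidable favourable error in the endpoint closest to the treatment's purpose.

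**What to change.** In the Statistical analysis plan section:

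- **OS:** keep the latest-news date.
- **Time to peritoneal relapse:** censor patients without that event, whether alive or dead, at the last disease assessment showing no peritoneal relapse. The present version can be shown as a sensitivity analysis.
- **RFS:** keep death from any cause as an event in the main analysis. Add a version that censors event-free patients at their last disease assessment and censors deaths after two or more missed visits at that assessment. Report it next to the latest-news version.
- State the assumption that stopping assessment is unrelated to relapse, and report how many patients in each arm were known alive beyond their last assessment. If that number is zero, the versions will nearly coincide.

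The cost is a few sentences. The dates come from visits already scheduled. The downside is slightly less follow-up and so slightly wider intervals, plus reliance on the stated assumption. This change does not deal with deaths as a competing event for peritoneal relapse, which is a separate matter.

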#### Toxicity monitoring

Sequential monitoring of mortality at 30 days (30D) will be performed in each treatment arm for each death (occurring before 30 days) once the second death has occurred. The 30D mortality rate post-surgery plus intraperitoneal chemotherapy was 6% in the recently published large French series [10]. Monitoring will be based on the one-sided exact binomial test at 10% of the following hypothesis: 30D mortality > 6%, without adjusting for multiple analyses which will be a maximum of 3 (no adjustment as a precaution). In the event of 2 deaths (before 30 days) occurring in 9 patients or fewer, or of 3 deaths (before 30 days) occurring in 18 patients or fewer, the treatment arm will be halted. If 4 deaths (before 30 days) are observed in the 20 patients included or fewer, mortality at 30 days will be considered too high and the treatment arm will be considered unacceptable.

The grade 3-4 toxicity rate at 30 days and the early surgical re-intervention rate at 30 days will also be evaluated in both treatment arms. The rate of grade 3-4 toxicity was 28% in the French surgery plus intraperitoneal chemotherapy series and the rate of early re-intervention was 26% [10]. An interim analysis will be performed on the first 10 patients in each arm and a final analysis on the 20 patients in each arm for each of these 2 endpoints. The analyses will be based on the one-sided exact binomial tests at 10% of the following hypotheses: for toxicity, rate of grade 3-4 > 30% and for early re-interventions, rate > 25%. For both endpoints, adjustment for the multiple analyses will be done using Pocock method.

### Quality assurance

The protocol will be conducted according to Good Clinical Practice (GCP) guidelines and to the ethical principles described in the Declaration of Helsinki. The study protocol was approved by the leading Ethics Committee and was subject to the approval of the national competent authority (ANSM, ref A120339-21) considered mandatory by federal law. The study was assigned the EudraCT number 2012-000475-174 and is registered at ClinicalTrials.gov (NCT01784900).

## Discussion

The peritoneum is one of the most frequent sites of recurrence from gastric carcinoma after curative treatment, despite the administration of pre- and/or postoperative systemic chemotherapy. In addition, the prognosis of peritoneal carcinomatosis from gastric carcinoma remains poor, and has not really been improved during recent years, despite the advent of targeted therapies. A meta-analysis reported that systemic chemotherapy extended median survival time to 11 months in patients with advanced gastric cancer compared to the best supportive care alone [25].

In an attempt to improve the prognosis of such patients operated on for gastric carcinoma, prophylactic HIPEC has been evaluated in patients at higher risk of developing peritoneal recurrence. A meta-analysis demonstrated that intraperitoneal chemotherapy combined with surgery yielded a positive effect on overall survival [26]. These results were confirmed in a recent large retrospective study of 360 patients with stage T2-4bN0-3 M0 gastric adenocarcinoma. It obtained a 5-year overall survival rate of 60.4% after surgery plus intraperitoneal chemotherapy compared to 42.9% when surgery alone was performed (p = 0.001) [27]. Whereas the prognosis of PC from colorectal cancer has changed with the development of locally administered HIPEC, survival results after HIPEC in the treatment of carcinomatosis from gastric cancer remain disappointing, yielding a 5-year survival rate of less than 20%.

Currently, there is no real effective treatment to offer to these patients. Innovative therapeutics are desperately required. The anti-tumour activity of catumaxomab has been demonstrated in vitro, in ascitic fluids from malignant ascites, notably from gastric carcinoma. A clinical effect on paracentesis-free survival and on the time to deterioration of QoL, has also been demonstrated in a randomised study [16]. Thus, the use of catumaxomab to treat microscopic residual disease after resection of peritoneal carcinomatosis from gastric carcinoma appears to be a good therapeutic option. The aim of the IIPOP randomized phase II study is to assess 2-year overall survival after complete resection of limited carcinomatosis (PCI ≤ 12) synchronous with gastric carcinoma, followed by intraperitoneal infusion of catumaxomab with different total doses administered in each of the 2 arms. Mortality, morbidity and specific toxicity will also be evaluated. In addition to these analyses, translational research will be conducted to determine immunological markers of the efficacy of catumaxomab and to correlate these markers with clinical efficacy.

## Abbreviations

PC: Peritoneal carcinomatosis; HIPEC: Hyperthermic intraperitoneal chemotherapy; Fab: Fragment antigen binding; EpCAM: Epithelial cell adhesion molecule; Fc: Fragment crystallisable region; IL: Interleukin; HAMAs: Human anti-mouse antibodies; SIRS: Systemic inflammatory syndrome; OS: Overall survival; ALAT: Alanine aminotransférase; ASAT: Aspartate aminotransférase; PCI: Peritoneal cancer index; CRF: Case report form.
